**Figure 1 figure1:**
[figure not shown]
Study design.

### Waitlist Condition

The attention control waitlist condition involves a comparable amount of phone contact to the intervention condition, with roughly 20 minutes of companionship calls per week. However, in the attention control, participants will not be exposed to CBT-related content. The purpose of companionship calls is to provide socialization and contact with supportive individuals without introducing structured therapeutic content.

### Discontinuation

Consented participants may still be deemed ineligible during study participation if they develop significant clinical worsening of depression, suicidal ideation, or other circumstances (eg, terminal illness or prolonged hospitalization) that preclude their ongoing involvement with the trial. Participants will be consulted regarding potential removal. Should a participant report suicidal ideation, a protocol will be in place that involves the participation of the study principal investigator and a clinical social worker. Should a participant’s circumstance interfere with their ongoing participation in the trial, the study team will discuss the risks and benefits of the participant’s ongoing involvement with the trial until a consensus is reached. If there is a clinically significant worsening of depressive symptoms, considerable effort will be made to expedite entry into the best available treatment outside the research protocol.

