### Study Design

Eligible and consented participants will be assigned either to an active treatment or a waitlist condition group that will cross over to the intervention at 10 weeks. A computer-generated random sequence will be used for assignment into either condition at a ratio of 1:1. Given the content of the intervention and study design, blinding the participant and evaluator to the condition will not be feasible.

All participants will be assessed using the same schedule. All will be invited to complete the comprehensive baseline assessment, postintervention or control assessment at week 10, and a follow-up assessment at week 20. Participants on the waitlist control will receive the intervention after their post-test at week 10 (Figure 1).

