### Measures

All measures are presented in Table 1. The primary clinical outcome in the study will be depressive symptoms as measured by the PHQ-9. The PHQ-9 is widely used in clinical research and has been used to evaluate older adults with medical and psychiatric illnesses in and outside of health care settings [43,44]. The PHQ-9 has been found to perform comparably to the Geriatric Depression Scale in identifying depression in older adults [45]. Scores on the PHQ-9 can range from 0 to 27 and indicate minimal, mild, moderate, moderately severe, or severe depression symptom severity. Sample items include “In the last week, have you had little interest or pleasure in doing things?” and “In the last two weeks, have you been feeling down, depressed, or hopeless?” Respondents indicate answers on a 4-point Likert scale ranging from “not at all” to “nearly every day.” In primary care patients, the measure has a sensitivity of 88% and a specificity of 88% [43]. The PHQ-9 will be administered at initial screening, baseline, after intervention, and 20-week follow-up. In addition, participants will complete a PHQ-9 self-assessment built into the web-based sessions every other week. To mimic the additional assessment patterns in the treatment group, participants in the control condition will also be administered the PHQ-9 every other week via phone during the 10-week waiting period.

**Table 1 table1:** Study measures and time points.

Variable	Assessment or activity	Screening	Baseline	Postrandomization			Follow-up
				Biweekly	Post		
Depression	PHQ-9^a^	✓	✓	✓	✓	✓	
Anxiety	GAD-7^b^		✓		✓	✓	
Social isolation	PROMIS-SI 8a^c^		✓		✓	✓	
Health self-assessment	PROMIS-GH^d^		✓		✓	✓	
Well-being and quality of life	EQ-5D-5L		✓		✓	✓	
Skill acquisition	CBTSQ^e^		✓		✓	✓	
Acceptability	Modified TEI^f^				✓		
Adherence	Session completion				✓		
Participant background	Sociodemographic, health status, and physical functioning	✓	✓				

^a^PHQ-9: Patient Health Questionnaire-9.

^b^GAD-7: Generalized Anxiety Disorder-7.

^c^PROMIS-SI 8a: Patient-Reported Outcomes Measurement Information System–Social Isolation 8a.

^d^PROMIS-GH: Patient-Reported Outcomes Measurement Information System–General Health.

^e^CBTSQ: Cognitive-Behavioral Therapy Skills Questionnaire.

^f^TEI: Treatment Evaluation Inventory.

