### Analytic Plan

To reduce bias, analyses will involve an intention-to-treat design. Linear mixed models will be used to test within-group changes over time and to compare changes between the treatment and control groups in outcomes of interest. The LASSO (least absolute shrinkage and selection operator [56,57]) variable selection technique will be used to find the optional selection of covariates for the final model. Exploration of mechanisms of change variables involves a procedure described by Hayes [58] that uses bootstrapping to test indirect effects. Statistical analysis will be conducted using Stata 15 SE. Although this trial is not fully powered for mediation analysis, findings from these analyses will inform future research to identify mechanisms of change.

We will use a pragmatic approach involving inductive and deductive coding for qualitative data. Qualitative analysis of the interview data collected from the completed single-group feasibility study is underway, and a codebook will be created during the process. The codebook from the single group study will serve as a framework for us to code the qualitative data collected from the pilot RCT. The codebook will be iteratively refined by reviewing the data and themes several times. Qualitative analysis will be conducted using Dedoose, a web app for mixed methods research.

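### The Discontinuation rule lets worsening depression lead to leaving the trial, not only the intervention, and is not reconciled with the common assessment schedule or the intention-to-treat analysis

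*Protocol article*

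**What the plan says.** Four parts of the protocol article bear on this.

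- **Discontinuation.** The rule reads: "Consented participants may still be deemed ineligible during study participation if they develop significant clinical worsening of depression, suicidal ideation, or other circumstances". The sentence gives terminal illness and prolonged hospitalisation as examples and ends with the qualifier "that preclude their ongoing involvement with the trial". Next comes "Participants will be consulted regarding potential removal", and risks and benefits are to be discussed until the parties agree. For worsening depression, "considerable effort will be made to expedite entry into the best available treatment outside the research protocol". No threshold for worsening is given. The section does not mention the outcome assessments of a participant who has been removed.
- **Study Design.** One assessment schedule applies to everyone, with invitations at baseline, week 10 and week 20. The same section says that "blinding the participant and evaluator to the condition will not be feasible".
- **Measures.** "The primary clinical outcome in the study will be depressive symptoms as measured by the PHQ-9".
- **Analytic Plan.** "To reduce bias, analyses will involve an intention-to-treat design", and "Linear mixed models will be used to test within-group changes over time and to compare changes between the treatment and control groups".

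**The concern.** Eligibility is settled before randomisation. Worsening of depression after that point is an outcome. The Discontinuation section treats it as a loss of eligibility and names the trial, not just the sessions or calls, as what the participant may leave. Read literally, the participants with the worst course are those whose later PHQ-9 scores are least likely to be obtained.

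Two features make such loss informative. The trigger is the construct of the primary outcome. The decision is also a judgement without a threshold, made by people who know the allocation. If the intervention works, more controls than treated participants would meet the trigger, so the loss could differ by arm. The Sample Size section assumes 20% attrition in both.

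An analysis plan can say how missing scores are handled, but it cannot recover scores that were never collected. Whether follow-up continues is settled by how this rule is worded and applied.

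**Working it through.** **1. The texts side by side.** Discontinuation permits removal from the trial for worsening. Study Design invites everyone at weeks 10 and 20. The Analytic Plan promises intention-to-treat. All three can hold together only if a removed participant is still invited and still analysed. No sentence says so, and the words for ineligibility and removal suggest otherwise. The rule speaks of consented participants, but it applies while they are taking part, which includes the time after randomisation.

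**2. Inputs from the plan (Sample Size).** Difference over 10 weeks: −0.8 × 5 = −4 PHQ-9 points. SD of change: 5. Attrition: 20% in each arm, which takes 52 to 52/0.8 = 65, as stated. The calculations below use only the −4 and the 5, plus the visit times and variances named in step 4.

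**3. If removed participants were excluded.** Assumptions not in the plan: change is normal with SD 5 in both arms; everyone whose change is at or above a cut-off c is removed and has no week-10 score; the rest are compared on mean change. With a = (c − μ)/5:

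- proportion removed = 1 − Φ(a)
- mean change of those left = μ − 5·φ(a)/Φ(a)

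Example with c = 5, control mean 0 and treatment mean −4:

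- Control: a = 1, removed 15.9%, mean 0 − 5·φ(1)/Φ(1) = −1.44.
- Treatment: a = 1.8, removed 3.6%, mean −4 − 5·φ(1.8)/Φ(1.8) = −4.41.
- Difference: −2.97, which is (4 − 2.97)/4 = 26% too small.

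If only half of those above the cut-off are removed, the means are −0.66 and −4.20 and the difference is −3.54.

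Over a range of assumptions (true difference −4 throughout):

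| Control mean change | Cut-off | Removed, control | Removed, treatment | Estimated difference |
|---|---|---|---|---|
| 0 | 3 | 27.4% | 8.1% | −2.52 |
| 0 | 5 | 15.9% | 3.6% | −2.97 |
| 0 | 8 | 5.5% | 0.8% | −3.53 |
| −2 | 3 | 15.9% | 3.6% | −2.97 |
| −2 | 5 | 8.1% | 1.4% | −3.37 |
| −2 | 8 | 2.3% | 0.3% | −3.76 |
| −4 | 3 | 8.1% | 1.4% | −3.37 |
| −4 | 5 | 3.6% | 0.5% | −3.66 |
| −4 | 8 | 0.8% | 0.1% | −3.90 |

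The direction depends on who is removed. In the worked example, removal in the control arm alone gives −4 − (−1.44) = −2.56. Removal in the treatment arm alone gives −4.41 − 0 = −4.41, an exaggerated effect. These are limiting cases; nothing in the article suggests that removal would be confined to one arm.

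**4. If the mixed model keeps data up to removal.** This was simulated with the plan's seven PHQ-9 times (weeks 0, 1, 3, 5, 7, 9, 10), linear trends and slope variance 0.2. Residual variance was 36 with intercept variance 4, or 9 with intercept variance 16. Control change over 10 weeks was 0 or −2. Removal was triggered by a recorded interim rise of 5 or 8 points from baseline. Estimated 10-week difference:

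| | True −4 | True 0 |
|---|---|---|
| Data up to removal kept | −3.95 to −4.01 | −0.04 to 0.04 |
| Removed participants excluded | −2.95 to −3.56 | −0.08 to 0.05 |

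With no removal at all, the same simulation gave −3.94 to −4.01, so the first row shows no bias beyond simulation error. The simulated removal rates (with a true −4, 11.1% to 60.5% of controls and 5.1% to 51.3% of treated) come from a mechanical trigger acting on noisy scores. They are not forecasts.

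**The case against.** The strongest reply is that the plan contains no conflict. The section concerns participation, not the analysis set. Removal is possible, not automatic, and follows consultation. The closing qualifier may govern the whole list, so that worsening counts only when continued involvement is ruled out. Study Design already invites everyone to weeks 10 and 20. A mixed model uses all scores recorded before removal, and step 4 shows that this can be enough. Finally, this is a journal article, and the full protocol or analysis plan may settle follow-up and missing data.

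Much of this stands, and it rules out several stronger readings that a reader might infer:

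- **That the rule contradicts intention-to-treat.** This is not supported. No sentence takes removed participants out of the analysis.
- **That worsening by itself removes a participant.** It does not; the rule is discretionary.
- **That a bias of about a quarter should be expected.** The 26% needs a cut-off that the plan does not give, removal of everyone above it, and a complete-case comparison that the plan does not describe.
- **That worsening is detected unequally because controls answer by phone and treated participants on the web.** This is conjecture. Measures adds the biweekly control PHQ-9 to match the treatment arm, and both arms receive weekly calls.

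Three things remain. First, the point concerns a rule that the article states, not a detail it omits. Second, the reassurance in step 4 requires removal to depend only on recorded PHQ-9. The section also allows suicidal ideation and judgement in discussion, in an unblinded trial. Third, participants who worsen are directed to outside treatment. A model fitted to their earlier scores projects the course they were on, whereas an intention-to-treat comparison asks for the course they actually had. Only continued assessment supplies that.

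**Conclusion.** The point holds as a failure to reconcile three sections. The Discontinuation rule can end trial participation for a reason that is itself the primary outcome, and nothing secures the later scores of those affected. The possible effect ranges from negligible (mixed model on data up to removal, with removal depending only on recorded PHQ-9) to a true −4 estimated at about −2.5 to −3.9 (removed participants excluded, the same cut-off of 3 to 8 points in both arms, control mean change 0 to −4). The second range rests on assumed cut-offs and on an exclusion that the plan does not state.

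When the same rule acts in both arms and removed participants are excluded, the bias is against the intervention, and in the simulation it vanishes when there is no true effect. Judgement applied differently by arm could push it either way. Neither size nor direction can be fixed from the article. The correction is worth making because it is cheap and must come before the data are lost.

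**What to change.** Leave the clinical response to worsening, suicidal ideation and illness exactly as it is; no view is taken here on when anyone should stop or what care should follow. Reconcile Discontinuation, Study Design and the Analytic Plan as follows:

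1. Replace the language of ineligibility and removal with discontinuation of the assigned condition (the sessions and coaching in one arm, the companionship calls in the other).
2. State that every randomised participant stays in the assigned arm and in the intention-to-treat analysis, with all recorded PHQ-9 scores.
3. State that those who discontinue are still invited to the week-10 and week-20 phone assessments unless they withdraw consent or are unable to take part.
4. Report the number discontinued for worsening, by arm.

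The cost is a change of wording and a few phone assessments that are already scheduled.

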### Clinical Management and Storage

All data related to the study (screening, pretest, coaching sessions, posttest, and follow-up) will be entered directly by project staff into REDCap [42]. During the active intervention, participants will be asked to fill out the PHQ-9 every other week, administered as a part of the web-based therapy lesson. These assessment data are stored in a HIPAA (Health Insurance Portability and Accountability Act)–compliant database hosted by the University of Michigan.

### Measures

All measures are presented in Table 1. The primary clinical outcome in the study will be depressive symptoms as measured by the PHQ-9. The PHQ-9 is widely used in clinical research and has been used to evaluate older adults with medical and psychiatric illnesses in and outside of health care settings [43,44]. The PHQ-9 has been found to perform comparably to the Geriatric Depression Scale in identifying depression in older adults [45]. Scores on the PHQ-9 can range from 0 to 27 and indicate minimal, mild, moderate, moderately severe, or severe depression symptom severity. Sample items include “In the last week, have you had little interest or pleasure in doing things?” and “In the last two weeks, have you been feeling down, depressed, or hopeless?” Respondents indicate answers on a 4-point Likert scale ranging from “not at all” to “nearly every day.” In primary care patients, the measure has a sensitivity of 88% and a specificity of 88% [43]. The PHQ-9 will be administered at initial screening, baseline, after intervention, and 20-week follow-up. In addition, participants will complete a PHQ-9 self-assessment built into the web-based sessions every other week. To mimic the additional assessment patterns in the treatment group, participants in the control condition will also be administered the PHQ-9 every other week via phone during the 10-week waiting period.

**Table 1 table1:** Study measures and time points.

Variable	Assessment or activity	Screening	Baseline	Postrandomization			Follow-up
				Biweekly	Post		
Depression	PHQ-9^a^	✓	✓	✓	✓	✓	
Anxiety	GAD-7^b^		✓		✓	✓	
Social isolation	PROMIS-SI 8a^c^		✓		✓	✓	
Health self-assessment	PROMIS-GH^d^		✓		✓	✓	
Well-being and quality of life	EQ-5D-5L		✓		✓	✓	
Skill acquisition	CBTSQ^e^		✓		✓	✓	
Acceptability	Modified TEI^f^				✓		
Adherence	Session completion				✓		
Participant background	Sociodemographic, health status, and physical functioning	✓	✓				

^a^PHQ-9: Patient Health Questionnaire-9.

^b^GAD-7: Generalized Anxiety Disorder-7.

^c^PROMIS-SI 8a: Patient-Reported Outcomes Measurement Information System–Social Isolation 8a.

^d^PROMIS-GH: Patient-Reported Outcomes Measurement Information System–General Health.

^e^CBTSQ: Cognitive-Behavioral Therapy Skills Questionnaire.

^f^TEI: Treatment Evaluation Inventory.

Anxiety will be assessed with the General Anxiety Disorder-7, which has been validated in populations of older adults [46]. Sample items include “How often have you been bothered by feeling nervous, anxious, or on edge in the last two weeks?” and “How often have you been bothered by worrying too much about different things in the last two weeks?” Like the PHQ-9, respondents answer on a 4-point Likert scale ranging from “not at all” to “nearly every day.” In primary care patients, the measure has a sensitivity of 89% and a specificity of 82% [47].

Social isolation will be measured using the Patient-Reported Outcomes and Measures Information System–Social Isolation (PROMIS-SI 8a). This measure has been used extensively in older adults with chronic health conditions and depression [48-50]. This 8-item measure uses a 5-point Likert scale with responses ranging from “always” to “never.” Sample items include “I feel isolated from others” and “I feel that people avoid talking to me.” The PROMIS-SI has high internal consistency (Cronbach α=.91) [51].

The PROMIS–General Health (PROMIS-GH) will be used as a global measure of health and health-related quality of life. This 10-item measure uses a 5-point Likert scale ranging from “excellent” to “poor.” It contains items such as “In general, would you say your health is...?” and “In general, how would you rate your satisfaction with your social activities and relationships…?” The PROMIS-GH has been validated in older adults with chronic health conditions, demonstrating moderate internal reliability (ordinal α=.82-.88) [52].

Quality of life will be measured using the EQ-5D-5L. Respondents answer on a 5-point Likert scale ranging from “I have no problems with…” to “I am unable to…/I have extreme…” They rate their experience in 5 life areas (mobility, self-care, usual activities, pain, and anxiety or depression). It also includes an overall health ranking on a scale of 0-100. In a systematic review including 99 studies that included a diverse range of medical conditions, the EQ-5D-5L exhibited overall excellent psychometric properties [53].

To explore the role of CBT skill acquisition, participants will complete the Cognitive-Behavioral Therapy Skills Questionnaire. This validated 16-item questionnaire assesses a respondent’s ability to apply cognitive restructuring, behavioral activation, and other CBT-related skills [54]. Participants are asked how often they currently do sample activities, such as making plans over the weekend, motivating themselves to do things, and socializing even though they do not want to. Items are answered on a 5-point Likert scale ranging from “I don’t do this” to “I always do this.”

Acceptability will be assessed by the number of sessions participants completed (ie, adherence) and the modified Treatment Evaluation Inventory. This 11-item inventory has been previously used to evaluate the acceptability of cognitive therapy for depression interventions among older adults and has good convergent validity and internal consistency (α=.92) [55]. The measure will be administered after the intervention. The measure is answered on a 5-point Likert scale ranging from “never” to “always.”

### Qualitative Interviews

After completing the intervention, participants will complete a semistructured qualitative interview lasting roughly 30 minutes. The interview probes several domains, including their experience with the program, likes and dislikes, and experience with specific program components (eg, storyline, home practice, materials, and ease of use). Additional questions will relate to participants’ relationship with their Empower Coach.

### Sample Size

A sample size of 70 (n=35 per group) should provide at least 80% power, allowing for a 20% attrition rate for both arms. Specifically, we considered the case where the 2 arms are compared in terms of weekly changes in the mean PHQ-9 survey responses between the baseline, 5 interim in-app PHQ-9 assessments (roughly at weeks 1, 3, 5, 7, and 9), and the 10-week follow-up PHQ-9 survey. We assume that the changes in the mean response can be expressed in terms of a linear trend, and the treatment effect can be expressed in terms of the difference in slopes or rate of change (δ = –0.8 × 5 in the total PHQ-9 score over 10 weeks; 5 is the SD in the change scores in our feasibility study). Sample size estimates used the following inputs: (1) type I error rate (α)=.05; (2) the smallest meaningful difference to be detected (δ) over the 10 weeks; (3) power (γ)=.80; (4) we assumed that outcome within-subject variance (σ^2^=6^2^; estimated from our feasibility study data) is constant over time; (5) the number of repeated measurements per person (n): 1 baseline, 5 in-app assessments, 1 final postbaseline for a total of 7 repeated assessments; and (6) regarding between-subject variation of the slopes, we assumed a variance of random slopes τ^2^=0.2 (estimated from our feasibility study data). The sample size is 52 for both arms with equal randomization probabilities; with an attrition rate of 20% for both arms, the total required sample size is 65. We set the final target sample size to 70 to allow room for higher attrition and lower adherence.

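### The inputs printed in the Sample Size section do not reproduce the stated 52: with σ²=6² the slope calculation needs about 118 evaluable, and the article does not show which number is wrong

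*Protocol article*

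**What the plan says.** The Sample Size section of the protocol article claims that 70 participants, 35 per group, "should provide at least 80% power, allowing for a 20% attrition rate for both arms". It compares the arms on a linear trend in PHQ-9, with the treatment effect expressed as a difference in slopes. The printed inputs are:

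- effect: "δ = –0.8 × 5 in the total PHQ-9 score over 10 weeks; 5 is the SD in the change scores in our feasibility study"
- error rate and power: "type I error rate (α)=.05" and "power (γ)=.80"
- residual variance: "we assumed that outcome within-subject variance (σ^2^=6^2^; estimated from our feasibility study data) is constant over time"
- random-slope variance: τ²=0.2, also attributed to the feasibility data
- seven assessments: baseline, five interim at roughly weeks 1, 3, 5, 7 and 9, and week 10

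The result is: "The sample size is 52 for both arms with equal randomization probabilities". Allowing for 20% attrition takes this to 65. The target is then rounded up to 70 to leave room for higher attrition and lower adherence.

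**The concern.** A difference-in-slopes calculation is fully determined by the effect, the two variance components, the visit times, α and power. All of these are printed except the sidedness of α, so the result can be checked. It comes out at more than twice the stated figure.

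The power statement is the stated justification for 70. If the printed variance is right, that statement is wrong, and a null result could be read as coming from an adequately powered test. If the variance is misprinted, the sample size may stand, but anyone planning the later fully powered trial from this paragraph would carry forward a residual variance six times too large.

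**Working it through.** **Inputs** (all from the Sample Size section)
- δ = 0.8 × 5 = 4 points over 10 weeks = 0.4 per week
- σ² = 6² = 36 and τ² = 0.2
- visits at weeks 0, 1, 3, 5, 7, 9, 10: mean 5, Σ(t−t̄)² = 25+16+4+0+4+16+25 = 90
- α = .05, taken as two-sided; power .80; (1.960+0.842)² = 7.849
- 1:1 allocation

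**Formula.** N(total) = 4 (z_α + z_power)² × [σ²/Σ(t−t̄)² + τ²] / δ²

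**Printed inputs**
- slope variance per person = 36/90 + 0.2 = 0.60
- N = 4 × 7.849 × 0.60 / 0.16 = 117.7, so 118 evaluable
- 118/0.8 = 147.5, so 148 enrolled at 20% attrition

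The plan's attrition step is correct: 52/0.8 = 65. The discrepancy lies in the 52.

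**Other readings with σ²=36 and τ²=0.2, one change at a time**

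| Reading | Total N |
|---|---|
| Seven equally spaced visits | 130 |
| One-sided α | 93 |
| Common-baseline mixed model, assumed intercept variance 5 to 36 | 79 to 102 |
| Common-baseline mixed model, zero intercept variance | 66 |

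None gives 52. Changing τ² does not rescue it either: reading 0.2 as an SD gives 86 (68 one-sided), and dropping the random slope altogether gives 79 (62 one-sided).

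One stacked combination does come close. In the zero-intercept-variance model the slope variance is 36/Σt² + 0.2 = 36/265 + 0.2 = 0.336. With one-sided α, (1.645+0.842)² = 6.183 and N = 4 × 6.183 × 0.336 / 0.16 = 51.9. This needs a one-sided test and no stable differences in PHQ-9 level between people. The article states neither. With an intercept variance of 5, the one-sided figure is already 62.

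**Routes that give 52 without such assumptions**
- σ² = 6 instead of 6²: 6/90 + 0.2 = 0.2667, and N = 4 × 7.849 × 0.2667 / 0.16 = 52.3.
- Two-sample t-test on change scores, difference 4, SD 5 (d = 0.8): 25.5 per arm, so 26 per arm and 52 in total. This uses neither σ², τ² nor the seven assessments.

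**Consistency of the variances.** Under the stated model, the variance of the week 0 to week 10 change is 2σ² + 10²τ², whatever the intercept variance.
- σ² = 36: √(72+20) = 9.6
- σ² = 6: √(12+20) = 5.7
- stated feasibility change SD: 5

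**Power, normal approximation, two-sided**

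| Basis | 52 evaluable | 56 evaluable | 70 evaluable |
|---|---|---|---|
| Slopes, σ²=36 | 46% | 49% | 58% |
| Slopes, σ²=6 | 80% | 83% | 90% |

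A simulated t-test on slopes at 56 evaluable gives 47.5% and 81.5%. The change-score t-test with d=0.8 has about 84% power at 56. The difference detectable with 80% power at 56 under σ²=36 is 10 × 2.802 × √(4 × 0.60/56) = 5.8 points.

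**The case against.** A reader might infer that the trial has only about 49% power. The article does not support that as a fact. The 49% holds only if 36 is the true residual variance, and the same paragraph argues against it: "5 is the SD in the change scores in our feasibility study", whereas σ²=36 implies 9.6. Both simple routes to 52 support the chosen size, with about 83% to 84% power at 56 evaluable. A misprinted input, or a calculation done by another method, is at least as plausible as an underpowered trial.

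The figure of 118 also rests on choices the article leaves open. Sidedness is not given, visit times are approximate, and the Analytic Plan names linear mixed models, which can use the baseline more efficiently and keep partial series from people who drop out. The 49% treats each dropout as contributing nothing; with no attrition it is 58%.

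Finally, the trial is presented as a pilot giving preliminary evidence, and small sample size is an acknowledged limitation.

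The objection succeeds in making the power loss conditional. It does not restore the calculation. Reaching 52 with σ²=36 takes two unstated assumptions together, one of them implausible, and even then the conflict with the change SD of 5 remains. Pilot status does not remove an explicit power claim.

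**Conclusion.** The paragraph is wrong as written. The printed inputs lead to about 118 evaluable under the standard two-sided slope formula, and to between about 66 and 130 under the one-sided, equal-spacing and common-baseline variants taken singly, against a stated 52. Separately, σ²=36 with τ²=0.2 cannot be squared with a change SD of 5, although σ², τ² and that SD are all attributed to the feasibility study.

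The article does not show which number is at fault: the printed σ², the 52, or the description of the method. Power at 56 evaluable is about 83% if σ²=6, about 84% if a t-test with d=0.8 was used, and about 49% if σ²=36 is real. These figures assume a two-sided 5% test and 20% attrition with no information from those who drop out.

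**What to change.** Check the feasibility-study output and restate the Sample Size paragraph so that inputs, method, sample size and power agree, including whether α is one- or two-sided.

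- If the residual variance is 6, print σ²=6 and keep 70, with power of about 83% at 56 evaluable.
- If it is truly 36, replace the 80% power claim with about 49% at 56 evaluable (58% with no attrition; detectable difference about 5.8 points at 56), and present the trial as an estimation pilot.
- If 52 came from a t-test with d=0.8, state that method and remove the slope inputs as its basis.

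In each case the printed σ², τ² and change SD should be reconciled with one another. The cost is one look at existing output and a reworded paragraph. The stated power may become less favourable, but no change in enrolment is needed.
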